### Methods in analysis to handle protocol non-adherence and any statistical methods to handle missing data {20c}

As this is a study in a healthcare setting and not a clinical trial testing a clinical procedure or medication, protocol non-adherence is not relevant here. For intention-to-treat analyses, it may become necessary to impute missing data because the intention-to-treat analysis includes all participants, regardless of their adherence to the study. If (potentially multiple) imputation of missing data will be required, it will be carried out especially in the analysis of the primary research question. Scores will be imputed, not individual items, and this will be done separately for each outcome or research question. For per-protocol analyses, missing data will not be a concern, as only participants who have completed all necessary measurements will be considered here. If significant group differences will occur at baseline, the inverse probability weighting procedure may become necessary.

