**Methods:**

UPlusE is a prospective, cluster-randomized controlled trial conducted in an outpatient setting. Obstetric and paediatric practices will be randomized into an intervention and control group (1:1 ratio). Practices and enrolling patients will be required to use specific smartphone apps (practice apps) for interaction. The screening will occur with the apps at each paediatric checkup up to the child’s age of 12 months, using the Edinburgh Postnatal Depression Scale (EPDS), KID-PROTEKT questionnaire, and the scale 1 (impaired bonding) of the Postpartum Bonding Questionnaire (PBQ-1). The goal is to screen 10,000 patients across Germany. Gynaecologists and paediatricians will receive certified training on peripartum depression. Participants in the intervention group with scores above cut-offs (EPDS ≥ 10, KID-PROTEKT ≥ 1, PBQ-1 ≥ 12) will receive counselling through their treating gynaecologists/paediatricians and will be provided with regional addresses for psychiatrists, psychotherapists, and “Frühe Hilfen” (early prevention) as well as family counselling centres, depending on symptom severity. At each screening, participants will be asked whether they sought support, where, and with whom (utilization). Utilization is the primary outcome.

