### Intervention description {11a}

The intervention is delivered to participants through the practice apps. These apps are established communication tools used for conveying practice information and communication, scheduling, or reminding appointments.

With the UPlusE module, the following interventions are being conducted:All participants receive information/guidance about childbirth and parent–child interaction through automatically sent push notifications. The intervention group gets more specific guidance; the control group gets unspecific information.All participants are screened regularly for depression, psychosocial stress, and impaired bonding (in parents) through questionnaires.All participants in the intervention group receive their screening result, subsequent information about peripartum depression, psychosocial distress, distress with their babies, and recommendations for treatment and/or counselling on special pages of the website www.upluse.de.Participants in the intervention group with a positive screening result receive their screening result with subsequent recommendations for treatment and/or counselling from their treating physician. Simultaneously, regional contact information for mental health practitioners, “Early Prevention” and counselling services, peers, and support groups are made available in the apps’ data pool.

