‘quite often’, ‘sometimes’, ‘rarely’, and ‘never’) [27].5.Questionnaire on Crying, Feeding, and Sleeping (SFS):For measuring infant regulatory disorders, the extended SFS questionnaire will be used, comprising 37 items about infant crying, sleeping, and eating behaviour [28]. Total mean scores above 1.84 (crying and sleeping) or above 1.27 (feeding scale) indicate regulatory problems. Six items based on DC: 0–5 (classification system for the diagnosis of mental disorders in infants, toddlers, and preschool children) will be used for further differentiation and clinical classification of symptoms related to excessive crying, sleep disorders, and early childhood feeding disorders.6.Questionnaire on treatment/counselling utilization:Utilization of treatment for mental health issues and counselling for psycho-social stress and parent-child bonding issues will be systematically captured via a project-specific questionnaire in the practice apps ‘My Gynaecology Practice’ and ‘My Paediatric Practice’ through self-report by the participants. The questionnaire assesses information about whether treatment/counselling has been sought. If utilization has occurred since the previous assessment, details such as the institution visited (pregnancy counselling centre, child protection coordination centres, ‘Early Prevention’ services, specialized outpatient clinic, psychiatrist/psychosomatics/psychotherapist, general practitioner, other), the motivating factor, and the referrer will be collected. As of our knowledge, specifically fitting standardized, validated, and publicly published questionnaires for this purpose are currently not available.7.Process analysis questionnaireTo identify technical and organizational barriers as well as facilitating factors for the implementation of the care model, a process evaluation will be conducted. This involves surveying all participating practices, mental health practitioners, and counselling services. Except for mental health practitioners and ‘Early Prevention’, the survey will be conducted using project-specific questionnaires via the practice apps ‘My Gynaecology Practice’ or ‘My Paediatric Practice’. Mental health practitioners and ‘Early Prevention’ services cannot be reached through the practice apps: for the process evaluation, these recipients will be invited to participate in the survey via email by the responsible contact persons from the study team. The survey will use a digital form. The questionnaires for process evaluation will be designed by the Institute for Community Medicine, University Medicine Greifswald, and will cover aspects such as:The number of participating practices, mental health practitioners, and ‘Early Prevention’ services.Their reasons for participation.The feasibility of implementing the intervention in their respective settings.Acceptance of the intervention.Perceived technical and/or organizational barriers or gaps in the implementation of the intervention.Benefits perceived by the involved practices, mental health practitioners, and ‘Early Prevention’ services due to the intervention,Factors promoting the implementation of the care model.

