### Methods for additional analyses (e.g. subgroup analyses) {20b}

As sensitivity analyses, per-protocol analyses will also be conducted. Per-protocol analyses consider only the results of those patients who received the intervention according to the study protocol. In the UPlusE project, per-protocol analysis will be performed with data from patients who were positively screened and actually sought assistance.

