## Discussion

Depression and other mental health burdens as well as psychosocial distress and impaired bonding are often unnoticed during the peri- and postpartum period [5, 18]. Gynaecologists and paediatricians regularly encounter individuals in this phase of life. Even though the guidelines for children and maternity care consider the need to recognize psychosocial burdens, physicians frequently fail to recognize the psychological burdens of the parents [18]. Paediatricians are specialists for children. The parents of the children are, strictly speaking, not their patients. Both, gynaecologists and paediatricians, are not trained deeply in diagnosing and treating mental health conditions and therefore have mostly insufficient knowledge, competence, time slots, and the tools to recognize and to respond to depression and psychosocial burdens in mothers/parents. UPlusE will provide the necessary knowledge through CME-certified online training and offer the instrument for a systematic and standardized screening of depression and psychosocial burdens. Gynaecologists and paediatricians will then be able to comply with the guidelines for children and maternity care. Because UPlusE will be using the already widely spread practice apps ‘My Gynaecology Practice’ and ‘My Paediatric Practice’, we anticipate a high willingness to participate among physicians and a relatively low additional workload in everyday practice.

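### The per-protocol set is defined by help-seeking, which is the primary endpoint, while the plan calls non-adherence irrelevant and names no per-parent record of counselling

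*Protocol article*

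**What the plan says.** Section {20c} of the protocol article states that "protocol non-adherence is not relevant here", on the ground that this is a study in a healthcare setting and not a test of a clinical procedure or drug.

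Section {20b} plans per-protocol analyses as sensitivity analyses and gives two descriptions of the set:
- The concept: "Per-protocol analyses consider only the results of those patients who received the intervention according to the study protocol".
- The working definition, in the next sentence: "per-protocol analysis will be performed with data from patients who were positively screened and actually sought assistance".

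Section {20c} adds a completeness condition for these analyses: "only participants who have completed all necessary measurements will be considered here".

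The abstract states: "Utilization is the primary outcome". Table 1 under Outcomes {12} agrees; it lists use of mental health and early-prevention services from a project-specific questionnaire.

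On the physician's part, Intervention description {11a} states: "Participants in the intervention group with a positive screening result receive their screening result with subsequent recommendations for treatment and/or counselling from their treating physician". On measurement, section {18a} begins the detailed utilization items with "If utilization has occurred since the previous assessment, details such as the institution visited". The motivating factor and the referrer belong to this conditional block.

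**The concern.** Two things do not fit together. If non-adherence were irrelevant, there would be no separate group who received the intervention as planned, and no per-protocol analysis to run. The protocol also has a section on adherence, {11c}, but it covers parents completing questionnaires and staying with their doctor. It does not cover whether the doctor gives the counselling.

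The working definition then replaces receipt of the intervention with seeking help. Help-seeking is what the intervention is meant to change, so the set is selected on the outcome. An analysis presented as a check on the primary result could not contradict or support it.

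What is at stake is interpretation. If the intention-to-treat comparison shows no difference, readers will ask whether counselling does not work or was often not given. The planned per-protocol analysis cannot answer that, and the per-parent items named in the article stop short of the group that matters most: screen-positive parents who used nothing.

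**Working it through.** **1. The plan's sample size, reproduced.** Inputs from Sample size {14} are 15% against 25%, power 0.80, design effect 1.725 and dropout 20%. The two-sided alpha of 0.05 is from section {20a}, and 1:1 allocation is from Trial design {8}. With pooled variance under the null and no continuity correction:

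n per arm = [1.96·√(2·0.20·0.80) + 0.8416·√(0.15·0.85 + 0.25·0.75)]² / 0.10² = (1.109 + 0.472)² / 0.01 ≈ 250

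This gives 500 in total, as stated. Then 500 × 1.725 / 0.80 = 1078, also as stated. The design effect is taken as given here.

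**2. Can the per-protocol set be formed as written?** Yes. Screening scores and help-seeking are both collected in the app. After the plan's dropout, 1078 × 0.80 / 2 = 431 screen-positive completers remain per arm. At the planned rates the set contains:

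| Arm | Completers | Rate | In the set |
|---|---|---|---|
| Intervention | 431 | 25% | about 108 |
| Control | 431 | 15% | about 65 |

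**3. What can the set show about the primary endpoint?** Membership requires having sought assistance, and the abstract treats seeking support as utilization. The rate is therefore 108/108 against 65/65, a difference of zero whatever the true effect. If seeking and using were counted slightly differently, both rates would still be close to 100%.

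**4. Who is in the control part of the set?** Control parents who found help in usual care. Sections {19} and {11b} withhold their screening results until U6. The exceptions are a positive answer on self-harm, an item signalling risk to the child, and clinical signs the doctor notices. Most of the 65 would not have been counselled under the study, so receipt of the intervention does not describe them.

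**5. Which named data bear on delivery of counselling?**

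| Source | Section | Limitation |
|---|---|---|
| Motivating factor, referrer | {18a} | asked only after service use |
| Parent acceptance questionnaire | {12}, Table 1 | intervention arm, once at U6; content not given |
| Practice survey | {12}, {18a} | months 33–35; not per parent |
| Billing of UPlusE services | {5d} | content not described |

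For a screen-positive parent who used no service, no named item says whether the doctor raised the result. At the planned rates that is 431 − 108 = 323 intervention parents.

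**6. Illustration of dilution.** Assume that a share f of screen-positive intervention parents is counselled, that the rest stay at 15%, and that 25% presumes full delivery. The intervention rate is then 0.15 + 0.10·f. At 250 effective parents per arm:

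| f | Intervention rate | Power |
|---|---|---|
| 1.0 | 25% | 0.80 |
| 0.8 | 23% | 0.63 |
| 0.7 | 22% | 0.52 |
| 0.5 | 20% | 0.31 |

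The documents give no value for f.

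**The case against.** **Non-adherence can be set aside in a pragmatic trial.** Trial design {8} evaluates the programme in normal care, and intention-to-treat takes everyone as randomized. Imperfect delivery is then part of the effect being estimated. This stands for the primary analysis. It does not stand for a plan that adds a per-protocol analysis.

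**The article is condensed.** The full protocol, the analysis plan and the questionnaires are not shown, and the item lists in {18a} are introduced as examples. A counselling item may exist. This stands, so the point about the missing record is conditional. The contradiction and the outcome-defined set rest on what the text states.

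**The help-seeking set may serve other questions.** Objectives {7} lists sensitivity questions on symptoms, the parent–child relationship and child regulation among parents who use mental health services. The set has some descriptive use there. Even so, it retains 25% of one arm and 15% of the other, so its members are not comparable by randomization.

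**Stronger readings the documents do not support.** A reader might infer:
- that the per-protocol analysis cannot be formed at all. It can, because {20b} defines it by variables that are collected.
- that a null result could not be told apart from non-delivery by any means. That is too absolute, given the referrer item, the U6 acceptance questionnaire, the process evaluation and possibly billing.
- that counselling rests with doctors who lack "insufficient knowledge, competence, time slots, and the tools". The Discussion uses those words for the situation before UPlusE, and goes on to describe the training and the screening instrument meant to change it.
- that the power figures forecast a loss. Under {11a}, intervention parents also get results, information and regional addresses through the app and website, so part of the intervention does not need the talk. Section {14} gives 25% as a rate for the intervention group and does not say that it presumes full delivery.

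**Conclusion.** The point holds in three parts of differing firmness.

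- **Firm:** the statement in {20c} conflicts with the per-protocol plan in {20b}.
- **Firm:** the set as defined is selected on the primary endpoint. It yields about 100% utilization in both arms, with roughly 108 and 65 parents at the planned rates, and cannot act as a sensitivity analysis of the primary comparison. The counts assume the plan's rates and dropout. The conclusion does not depend on them.
- **Conditional:** the article names no per-parent record of counselling for parents who used no service, so a null result would be hard to separate from non-delivery. This holds unless the full protocol or the unseen questionnaires contain such an item.

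The power figures of 0.63, 0.52 and 0.31 show only that incomplete delivery could matter, on the two assumptions in the illustration. The primary intention-to-treat analysis stands. The change should be made because it is cheap and protects the interpretation of the main result.

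**What to change.** 1. Delete the sentence in {20c} that calls non-adherence irrelevant, and make {20b} and {20c} agree.
2. Define the per-protocol set by receipt of the intervention: screen-positive intervention parents for whom counselling was delivered, compared with screen-positive control parents, adjusted for baseline covariates. Call it supportive, since counselled parents are no longer a randomized group. Any analysis of parents who sought help should be labelled descriptive and kept to the secondary outcomes.
3. If no such item exists, add one yes/no app question, at least in the intervention arm: did the doctor discuss the screening result and recommend support? Cross-check it against UPlusE billing if the billing content allows.
4. In the control arm, a question worded for usual care could be asked once, at U6. Asking it at every visit may itself prompt help-seeking.
5. Report delivery by practice.
6. A complier-average estimate with allocation as instrument should be left out or labelled exploratory. Allocation also acts through app and website content, so the exclusion assumption is doubtful.

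The cost is one short app item, a few sentences in the analysis plan and one delivery table. Data management {19} already foresees changes to the user interface. Recruitment began on 9 February 2024, so a new item would cover only questionnaires still to come. The date of its introduction should be reported.

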### Outcomes {12}

The primary and secondary endpoints, as well as the parameters of the process evaluation, are presented in Table 1 along with the time points for assessment and measurement methods.

**Table 1 Tab1:** Primary and secondary outcomes UPlusE evaluation

Primary endpoint	Measurement	Time points	Methods
Utilization of services from mental health practitioners/"Early Prevention"	Project-specific questionnaire	From inclusion to U6 checkup	Apps ‘My Paediatric Practice’, ‘My Gynaecology Practice’, all participating parents
Secondary endpoints			
Depression/severity of depression	EPDS (Edinburgh Postnatal Depression Scale)	From inclusion to U6 checkup	Apps (as above), all participating parents
Parent–child bonding	PBQ (Postpartum Bonding Questionnaire)	From inclusion to U6 checkup (child's age of 10–12 months)	Apps (as above), all participating parents
Psychosocial burden	KID-PROTEKT questionnaire	From inclusion to U6 checkup (child’s age of 10–12 months)	Apps (as above), all participating parents
Child regulation	Extended SFS questionnaire	From inclusion to U6 checkup (child’s age of 10–12 months)	Apps (as above), all participating parents
Stigmatization	Project-specific questionnaire	Inclusion and U6 checkup (child’s age of 10–12 months)	Apps (as above), all participating parents
Process evaluation, participant acceptance/satisfaction	Project-specific questionnaire	At U6 checkup (child’s age of 10–12 months)	Apps (as above), parents in the intervention group
Process evaluation, acceptance/satisfaction of participating practices	Project-specific questionnaire	After completion of implementation phase (months 33–35)	Apps (as above), all participating gynaecological and paediatric practices
Process evaluation, acceptance/satisfaction of mental health practitioners/ ‘Early Prevention’	Project-specific questionnaire	After completion of implementation phase (months 33–35)	All involved mental health practitioners/ ‘Early Prevention’ services
Utilization of services in the healthcare system	Analysis of data from the participating health insurance funds	After completion of implementation phase	Data from all participating parents and children
Healthcare system costs in the first year after childbirth	Analysis of data from the participating health insurance funds	After completion of implementation phase	Data from all participating parents and children

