### Participant timeline {13}

Depending on entry point (enrolment into the study during pregnancy or at U3-, U4- or U5-checkup) and potential screening point at which a participant in the intervention group screens positive and is motivated for treatment, the duration of the intervention with follow-up observation varies between 6 and 15 months. The intervention is carried out up the U6-checkup (at child’s age 10 to 12 months). The participant timeline is depicted in Fig. 3.

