### Sample size {14}

The proportion of all parents who avail themselves of any mental health services is based on the available figures. (18% [22], health insurance data: 10–12%) and is assumed to be 15% in the following. The assumption is that through the intervention, the proportion of affected parents using mental health services can be increased to at least 25% in the intervention group. With *α* < 0.05 and a power of 0.80, a sample size of 500 subjects is therefore required. The cluster-randomized controlled design must be considered when calculating the required number of participants. The design effect due to cluster randomization is estimated at 1.725 (intra-cluster correlation (ICC): 0.15; number of patients/practices: 2.5). With a dropout rate of 20%, the number of required positively screened subjects is (500 × 1.725) / 0.80 = 1078. Given a known prevalence of peripartum depression of 10–15% as the condition that is in our focus, a total of 10,000 parents (5000 each in the intervention and control groups) must be screened and included (Fig. 3).

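### Keeping only completers does not make missing data harmless in the per-protocol analyses, and the help-seeking condition on the same set leaves utilization with nothing to compare

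*Protocol article*

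**What the plan says.** All references are to the protocol article.

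- **Role, section {20b}:** "As sensitivity analyses, per-protocol analyses will also be conducted".
- **Who is in the set, section {20b}:** first in general terms, "Per-protocol analyses consider only the results of those patients who received the intervention according to the study protocol", then specifically for this trial, "per-protocol analysis will be performed with data from patients who were positively screened and actually sought assistance".
- **Missing data in that set, section {20c}:** "For per-protocol analyses, missing data will not be a concern, as only participants who have completed all necessary measurements will be considered here". The article does not say which measurements are necessary.
- **Intention-to-treat, sections {20a} and {20c}:** multilevel analyses of all participants, with imputation of scores only if it proves to be required.
- **How utilization is captured, sections {11a} and {18a}:** by self-report in the app questionnaires sent before each checkup, asking about the time since the last one: "If utilization has occurred since the previous assessment, details such as the institution visited".
- **Entry, section {13}:** "enrolment into the study during pregnancy or at U3-, U4- or U5-checkup".
- **Planned loss, section {14}:** "With a dropout rate of 20" per cent.

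**The concern.** Section {20c} treats missing data as solved once incomplete participants are left out. Leaving them out hides the gaps. It does not make those who remain representative of those who left. The statement is also more than a detail deferred to an analysis plan: it is a positive claim that no handling is needed, and it closes the question in advance.

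The protocol gives reasons to expect that completion is not random. Physicians and parents know their arm ({17a}). Apart from safety notices given in both arms, only intervention parents receive results and counselling before U6 ({11a}, {11b}). The contractual duty to fill in questionnaires is stated to bind at least BKK members, while members of other insurers may also take part ({11c}, {18b}). A parent who becomes more depressed may also simply stop answering.

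At stake is what the per-protocol results can be used for. A sensitivity analysis with its own unexamined selection cannot reassure a reader about symptoms, bonding or child regulation. On utilization it has nothing to say.

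**Working it through.** **1. The plan's own loss figure.** Section {14} gives 500 subjects, design effect 1.725 and 20% dropout: 500 × 1.725 = 862.5, and 862.5 / 0.80 = 1078.1, which matches the stated 1078. (The design effect is taken as stated; whether it follows from its own inputs is a separate matter.) The plan thus expects to lose 1078.1 − 862.5 ≈ 216 positively screened parents. Missing data are part of its own expectations.

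**2. What can be missing.** Section {18b} allows a questionnaire to be submitted only when every item is answered. Gaps are therefore whole questionnaires or dropout, which are the events on which a completer rule selects.

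**3. The set that results.** Sections {20b} and {20c} together require that a parent (a) screened positive, (b) sought assistance and (c) completed the necessary measurements. Conditions (b) and (c) are determined after randomisation, and (b) is the primary endpoint. Using the planning rates of 15% and 25% and half of 1078 = 539 per arm:

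| | Control | Intervention |
|---|---|---|
| Positively screened | 539 | 539 |
| Sought assistance | 539 × 0.15 ≈ 81 | 539 × 0.25 ≈ 135 |
| Also retained, if the 20% loss is unrelated to help-seeking | 81 × 0.80 ≈ 65 | 135 × 0.80 ≈ 108 |

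If nobody is deterred by the intervention (an assumption), (25 − 15) / 25 = 40% of intervention help-seekers are parents who would not have sought help under usual care. The control set has no such parents. The two sets differ in composition before any questionnaire is missed, and the completer rule then selects again within them.

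**4. Utilization in this set.** Condition (b) applied in both arms gives 100% − 100% = 0, whatever the intervention does. Applied in the intervention arm only, it gives 100% against the planning value of 15%, an 85-point gap fixed by definition. Neither is an effect estimate.

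**5. Other outcomes in this set.** Take a binary U6 outcome with true proportion p in one arm. Let c1 be the completion probability among parents with the outcome and c0 among those without. Completers show

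p* = p·c1 / (p·c1 + (1 − p)·c0).

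This equals p only if c1 = c0 (for p strictly between 0 and 1). If c1 > c0 the proportion is overstated, and if c1 < c0 it is understated. When the pattern differs between arms, the difference between arms can shift either way. The article gives no values for c1 and c0, so neither sign nor size can be computed.

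**The case against.** The strongest defence is that little depends on this sentence. The per-protocol analysis is labelled a sensitivity analysis, the main analysis is intention-to-treat with imputation if needed, reminders and a contractual duty support completion, and the meaning of necessary measurements may be set out in an analysis plan that is not shown. The sensitivity questions in section {7} (symptom improvement, parent–child relationship and child regulatory problems among service users) also suggest that this set may never have been meant to re-estimate the utilization effect. All of this limits the consequences. It does not make the reasoning in {20c} correct, because those same outcomes are exposed to loss related to severity.

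Two stronger readings are tempting, and the documents do not support either.

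*Late entrants are over-represented.* A reader might note that a pregnancy entrant has four later questionnaires to complete and a U5 entrant only one. Assume equal entry shares, equal missingness per questionnaire and 20% overall non-completion (8.7% per questionnaire). Completion is then 0.694, 0.760, 0.833 and 0.913 for pregnancy, U3, U4 and U5 entrants, and the U5 share rises from 25% to 0.913 / 3.200 = 28.5%. But the set also requires help-seeking, and early entrants have longer to seek help. With a constant uptake rate averaging 25% (0.357, 0.283, 0.221 and 0.139 by entry point), the U5 share is 0.913 × 0.139 / (0.694 × 0.357 + 0.760 × 0.283 + 0.833 × 0.221 + 0.913 × 0.139) = 0.127 / 0.774 ≈ 16%. It stays at about 15–20% for overall non-completion of 10–40%. Under these assumptions late entrants are under-represented. The entry mix and the missingness are not in the documents, and the necessary measurements could mean entry and U6 only, so no direction should be claimed.

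*The utilization difference is inflated by a known amount.* A reader might apply the formula in step 5 to the planned 15% and 25%. In the set that {20b} defines, everyone sought assistance, so such a bias cannot arise there.

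**Conclusion.** The point holds in a limited form. The statement that missing data need no attention in the per-protocol analyses is wrong, because it rests on a complete-case restriction on a post-randomisation event in an open trial. Combined with the help-seeking condition, it yields a set in which utilization is 100% by construction and in which symptom, bonding and child-regulation comparisons can be biased in either direction.

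The 100% follows from the text alone. The 40% difference in composition rests on the planning rates and on nobody being deterred by the intervention. The magnitude and sign of any bias from non-completion cannot be derived from the documents. Only the sensitivity analysis is affected. The point is worth correcting before analysis, but it does not threaten the primary intention-to-treat result.

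**What to change.** 1. In {20c}, delete the sentence on per-protocol missing data and the completer condition.
2. In {20b}, define the per-protocol set by delivery of the intervention as planned, not by help-seeking or questionnaire completeness. State a parallel definition for controls, for example positively screened parents whose results were not routinely fed back before U6, as the protocol already foresees.
3. Handle missing scores in that set with the same multilevel model or multiple imputation as the intention-to-treat analysis, with arm and entry point included.
4. Report the share with complete data by arm and entry point.
5. Present the result as supportive. A delivery-based set is still selected after randomisation, although no longer on the outcome.

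The cost is a change of wording and modest extra analysis work. The work is not free, since imputation is only conditional in the current plan and would have to be specified. The fix also assumes that delivery of feedback and counselling is recorded for each participant. The article does not say so, and this should be confirmed first.
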